## Abstract

**Background:**

Irritable bowel syndrome (IBS) is a common gastrointestinal functional disease. Adults with IBS may experience abdominal pain, change of bowel habits, and abnormal stool form without organic disease. IBS can seriously affect their work productivity and quality of life, especially diarrhea-predominant irritable bowel syndrome (IBS-D). The Chinese medicine JCM-16021 has been shown to be potentially effective in improving the symptoms of IBS-D based on a small scale clinical trial. Hence, a large scale clinical study is designed to further evaluate the efficacy and safety of the Chinese medicine JCM-16021 for IBS-D with traditional Chinese medicine (TCM) pattern of Liver Stagnation and Spleen Deficiency (LSSD).

**Methods:**

This study is a multi-center, randomized, double-blind, placebo-controlled clinical trial. 392 eligible participants will be enrolled with 2-week run-in, 8-week treatment and 8-week follow-up. After run-in period, participants will be randomized to receive either the Chinese medicine JCM-16021 or placebo for 8 weeks, and will have post-treatment follow up for another 8 weeks. The primary outcome is the improvement rate on the global assessment of improvement (GAI) at week 10. The secondary outcomes consist of changes of IBS-D symptoms, TCM pattern improvement, IBS-Quality of Life (IBS-QoL), IBS-Symptom Severity Score (IBS-SSS), safety, etc.

**Results:**

A standard protocol has been developed for the study. The protocol will provided a detailed procedure to conduct a clinical trial and verify if the Chinese medicine JCM-16021 would significantly improve the overall symptoms of IBS-D with LSSD pattern of TCM by relieving abdominal pain, reducing stool frequency, improving the stool consistency and improving quality of life. The consolidated evidence from the study can shed light on the treatment of IBS-D with Chinese medicine.

**Conclusion:**

The protocol will provide details for investigators about the study following SPIRIT Statement. High-quality evidence on the efficacy and safety of Chinese medicine JCM-16021 for IBS-D will be provided through strict compliance with the protocol.

*Trial registration*: ClinicalTrial.gov identifier: NCT03457324. Registered 8 February 2018, https://clinicaltrials.gov/ct2/show/NCT03457324?term=NCT03457324&draw=2&rank=1

**Supplementary Information:**

The online version contains supplementary material available at 10.1186/s13020-021-00530-2.

## Background

Irritable bowel syndrome (IBS) is a common functional gastrointestinal disorder, which is diagnosed on the basis of recurrent abdominal pain related to defecation or in association with a change in stool frequency and form [1]. Furthermore, no anatomical causes have been found 2]. According to a meta-analysis, the pooled estimate of international IBS prevalence is about 11.2% [3]. In Hong Kong, based on Rome II criteria, the prevalence was reported to be 6.6%, of which the proportion of diarrhea-predominant irritable bowel syndrome (IBS-D) was 27% [4].

The pathogenesis of IBS is currently unclear as none of its anatomical causes could be found. It is caused by multiple factors, which include psychological factors, changes in gastrointestinal motility, neural and endocrine factors, infection, diet, drugs etc. [5, 6]. Under the influences of the above factors, the intestinal function is disturbed and that causes abdominal pain, abdominal bloating, constipation or diarrhea. At present, the more accepted mechanisms of IBS include visceral hypersensitivity, abnormal gut motility, abnormal fecal transmission, and mental factors [7]. Recently, some studies show that IBS-D is the most common subtype in IBS based on Rome IV criteria [8–10].

IBS-D greatly affects the quality of life of people. Individuals suffering from IBS-D always complain that they have to avoid traveling or going out because of concerns about toilet access [11]. However, there is still no very satisfactory therapy or medicine for IBS-D yet. According to a survey in America, people’s satisfaction with both over-the-counter (OTC) and prescription treatments for IBS-D are low, with about 20% and 25% of participants being very satisfied with OTC and prescription treatment, respectively [12]. Another study of IBS-D also showed that the overall treatment satisfaction was only approximately 20% [13]. In recent years, more and more people have tried to treat their symptoms with traditional Chinese medicine (TCM), which has been evaluated in many clinical studies [14]. A meta-analysis indicated that Chinese medicine was associated with the improvements of global symptom, IBS-Symptom Severity Score (IBS-SSS), and IBS-D symptoms [15].

According to the TCM theory, the Liver Stagnation and Spleen Deficiency (LSSD) is believed to be the major mechanism of IBS-D. The Liver governs Qi movement, and the Spleen Qi can maintain the transportation of water and nutrient throughout the whole body. Liver Qi stagnation affects the proper operation of the Spleen. When the Spleen is offended by Liver Qi Stagnation, diarrhea will occur. Therefore, the treatment should base on soothing the Liver Qi and strengthening the Spleen Qi. The Chinese medicine JCM-16021 is a new Chinese medicine formula composed of seven herbs: *Rhizoma Atractylodis Macrocephalae* (Baizhu) 20 g, *Radix Paeoniae Lactiflorae* (Baishao) 15 g, *Cortex Magnoliae Officinalis* (Houpo) 10 g, *Semen coicis Lachryma-jobi* (Yiyiren) 20 g, *Polygonaceae* (Huotanmu) 20 g, *Fructus Terminaliae Chebulae*(Hezi) 10 g, *Rhizoma Corydalis Yanhusuo* (Yanhusuo) 15 g. It is developed based on Chinese medicine theories and clinical experience and aims to soothe the Liver Qi and strengthen the Spleen Qi and hence treat IBS-D with LSSD pattern. Our previous small scale study indicated that the Chinese medicine JCM-16021 has a potential therapeutic effect on the relief of IBS-D symptoms compared to holopon and placebo [16]. Further, the Chinese medicine JCM-16021 can dose-dependently attenuate visceral hyperalgesia in neonatal maternal separation (NMS) rats by changing the synthesis and metabolism of 5-HT in the colons [17]. Another study also has indicated that the Chinese medicine JCM-16021 can reduce the colonic enterochromaffin (EC) cell hyperplasia and serotonin (5-HT) availability and upregulate the decreased levels of certain mucosal cytokines, especially the T-cell type 1- (T_h_1-) related cytokines in post-inflammation IBS rats [18]. Based on these studies, we hypothesize that the Chinese medicine JCM-16021 will be an effective remedy for IBS-D. This protocol can provide details for investigators about the study following the Standard Protocol Items for Clinical Trials with Traditional Chinese Medicine 2018 (SPIRIT-TCM Extension 2018), while the final study results will be reported following the CONSORT Extension for Chinese Herbal Medicine Formulas (CONSORT-CHM Formulas 2017) [19–21].

## Objective

The major objectives of this study are as follows: (1) investigate the efficacy of the Chinese medicine JCM-16021 for IBS-D participants with LSSD pattern of TCM; and (2) assess the safety of the Chinese medicine JCM-16021.

## Methods/design

The study is a multi-center, randomized, double-blind, placebo controlled clinical trial. In total, the whole study will last for 18 weeks and schedule five visits, including 2 weeks of the run-in period, 8 weeks of the treatment period, and 8 weeks of the follow-up period. At week 0, the first screening visit will be conducted to include potential participants. Week 0–2 belongs to run-in period. At week 2, the second visit will be conducted to assess the baseline of participants. Then, those eligible participants will be randomized in 1:1 ratio to receive either the Chinese medicine JCM-16021 or placebo. At week 6, the third visit will be conducted to assess the situation after treatment of 4 weeks. At week 10, the fourth visit will be conducted to assess the situation after treatment of 8 weeks. Then, these participants will be followed up with another 8-week to assess the situation after stopping the medicine and the fifth visit will be conducted at week 18. Participants will be assessed on the scheduled day for each visit by face to face at the designated clinics. The flowchart and schedule of the trial are shown in Figs. 1 and 2, including schedule of enrolment, interventions and assessments. The trial protocol is written in accordance with SPIRIT-TCM Extension 2018 checklist [14] (Additional file 1). And the structured study summary is described in Table 1 according to the World Health Organization Trial Registration Data Set.

**Fig. 1 Fig1:**
[figure not shown]
Flow chart

**Fig. 2 Fig2:**
[figure not shown]
The schedule of enrolment, interventions, and assessments. *GAI: Global Assessment of Improvement; §IBS: Irritable Bowel Syndrome; †TCM: Traditional Chinese Medicine; ‡IBS-QoL: Irritable Bowel Syndrome-Quality of Life; IBS-SSS**: Irritable Bowel Syndrome-Symptom Severity Score

**Table 1 Tab1:** WHO trial registration data set—structured summary

Data category	Information
Primary registry, trial identifying number	ClinicalTrials.gov (NCT03457324)
Date of registration in primary registry	February 8, 2018
Secondary identifying numbers	
Sources of monetary support	Innovative Technology Commission of the government of Hong Kong Special Administrative Region
Contact for public queries	[name], MD, PHD [[contact]]
Contact for scientific queries	[name], MD, PHD [[contact]]
Public title	Efficacy and Safety of Chinese Medicine JCM-16021 for Diarrhea-predominant Irritable Bowel Syndrome
Scientific title	Efficacy and Safety of Chinese Medicine JCM-16021 for Diarrhea-predominant Irritable Bowel Syndrome: Study protocol for a Multi-center, Randomized, Double-blind, Placebo Controlled Clinical Trial
Country of recruitment	Hong Kong, China
Health problem	Diarrhea-predominant Irritable Bowel Syndrome
Intervention(s)	Experimental group: JCM-16021 granules (8 g/sachet for each time, three times daily for 8 weeks)
	Control group: Placebo granules (8 g/sachet for each time, three times daily for 8 weeks)
Key inclusion and exclusion criteria	Inclusion criteria: (1) the diagnosis criteria of IBS-D; (2) the diagnosis of LSSD; (3) Age of 18–65 years; (4) with written informed consent
	Exclusion criteria: (1) Constipation predominant, mixed or unsubtyped IBS; (2) Abnormal colonoscopy within 5 years (except for benign polypectomy or hemorrhoids); (3) With severe diseases on the system of heart, lung, liver, and kidney which are diagnosed by TCM theory; (4) Concomitant diabetes, Glucose-6-Phosphate Dehydrogenase deficiency, unstable hypertension, malignant tumor or have undergone thyroid surgery or medication within a year; (5) With diseases on the spleen-stomach system or other diseases that affect the movement of qi on the spleen-stomach system, which are diagnosed by TCM theory; (6) Current concomitant medication with effects on gastrointestinal function (e.g. anticholinergic drugs, calcium channel blockers, 5-HT3 receptor antagonists, antidiarrheal agents, antacids, prokinetic agents, antidepressants, anxiolytics and intestinal flora regulating drugs); (7) Medical history of gastrointestinal surgery (except for appendicitis surgery); (8) The serum levels of alanine transaminase (ALT), aspartate transaminase(AST), and creatinine(Cr) exceed 1.5 times of the reference limit; (9) History of allergy in Chinese medicine; (10) Women in pregnancy or breast-feeding; (11) Medical history of neurological diseases or psychiatric disorders; (12) Currently participating in another clinical trial; (13) Taking IBS treatment drugs within 1 week
Study type	Interventional allocation: randomized
	Intervention model: parallel assignment
	Masking: double blind (participants and Physicians, Chinese Medicine Practitioners and research assistants)
	Primary purpose: Treatment
	Phase III
Date of first enrollment	October 2018
Target sample size	392
Recruitment status	Completed
Primary outcome	The improvement rate on the Global Assessment of Improvement (GAI) at week 10
Key secondary outcomes	Changes of IBS symptoms, TCM pattern improvement, IBS-Quality of Life (IBS-QoL), IBS-Symptom Severity Score (IBS-SSS), safety

### Setting of the study

The study will be simultaneously conducted in three centers, namely Hong Kong Baptist University Mr. and [name] Yin Chinese Medicine Specialty Clinic and Good Clinical Practice Centre, Hong Kong Baptist University HK Island Wei Ke Qiang Chinese Medicine Specialty Clinic, and Center for Integrative Medicine, Hong Kong Institute of Integrative Medicine, The Chinese University of Hong Kong.

### Randomization

The randomization sequence will be generated using block randomization with a fixed block size by our statistician with SPSS statistical analysis software. The sequence will be kept in opaque sealed envelopes with consecutive numbers. These envelopes will be prepared by pharmaceutical company. The envelopes numbered 001–100 and 201–392 will be kept at the site of Hong Kong Baptist University. The envelopes numbered 101–200 will be kept at the site of the Chinese University of Hong Kong. Chinese medicine practitioners responsible for the recruitment and evaluation will be blinded. Each center will have a research assistant responsible for allocating drugs to participants. The research assistant will open the same numbered envelope based on the randomization enrolment number when an eligible participant can be included in the trial. Then, the research assistant will assign the drugs to the participant according to the sequence. The eligible participants will be randomized and assigned to the Chinese medicine JCM-16021 group or the placebo group in 1:1 ratio (196 cases/group).

### Blinding

The trial is a double-blinded design, in which all the Chinese medicine practitioners, research assistants and participants are ignorant of the treatment assignments. The physical appearance of placebo is consistent with the Chinese medicine JCM-16021, including the packaging, appearance, color and taste. Pharmaceutical company will be responsible for labelling the Chinese medicine JCM-16021 and placebo according to the blinding codes. ‘16021A’ and ‘16021B’ will be used to label the interventions. The blinding code will be kept strictly confidential by the principal investigators until completion of the final statistical analysis and report of the trial. Only if there is a serious adverse event (SAE) relevant to the research medication, the assignment code will be broken. The date and reason for breaking the blinding code should be recorded in the case report form (CRF). Relevant institutions, including the Research Ethics Committee of Hong Kong Baptist University and Department of Health of Hong Kong Special Administrative Region should be informed accordingly within 24 h.

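### With only two arm-level drug labels, and the code held by the principal investigators, any single code break decodes both arms instead of one participant

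*Protocol article*

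**What the plan says.** **Labels.** The Blinding section states that the codes 16021A and 16021B "will be used to label the interventions. The blinding code will be kept strictly confidential by the principal investigators", and that "Pharmaceutical company will be responsible for labelling the Chinese medicine JCM-16021 and placebo according to the blinding codes". These are the only drug codes the article describes.

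**Custody and breaking.** The same section says: "The blinding code will be kept strictly confidential by the principal investigators until completion of the final statistical analysis and report of the trial". It continues: "Only if there is a serious adverse event (SAE) relevant to the research medication, the assignment code will be broken". The date and reason for a break must be entered in the case report form (CRF).

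**Who is blinded.** It says that "all the Chinese medicine practitioners, research assistants and participants are ignorant of the treatment assignments". The principal investigators are not named there or in the masking entry of Table 1. Under Quality control and assurance, a monthly meeting reports recruitment, compliance and adverse events to them.

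**Dispensing.** Under Randomization, the sequence is generated "using block randomization with a fixed block size by our statistician"; the size is not given. Envelopes 001–100 and 201–392 are kept at Hong Kong Baptist University, and 101–200 at the Chinese University of Hong Kong. A research assistant opens the envelope with the participant's number, and then "the research assistant will assign the drugs to the participant according to the sequence".

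**Outcomes.** GAI at week 10 is the participant's own rating, and slight improvement counts as success (Primary outcome). Investigators grade the cardinal symptoms and the TCM pattern (Secondary outcomes).

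**The concern.** When every supply in an arm carries the same letter, the assignment code is a single fact: which letter is active. It cannot be disclosed for one participant without being disclosed for all. The numbered envelopes do not help, because they are opened at enrolment to dispense drug and so cannot serve as individual emergency envelopes.

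Research assistants work with these letters participant by participant, so anyone told the meaning of a letter can learn many arms through them. The code holders also follow compliance and adverse events month by month.

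At stake is the credibility of the double blind for a subjective primary outcome and for several investigator-graded secondary outcomes. Knowledge of the arm could shift ratings made after a break.

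**Working it through.** **1. Where 392 comes from.** Inputs from Sample size calculation: a 15-point difference, 80% power, two-sided 5% alpha and 15% drop-out. The placebo rate is not stated. Taking the earlier comparator rate of 32% gives 32% against 47%, mean 39.5%.

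n per group = [1.960·√(2·0.395·0.605) + 0.842·√(0.32·0.68 + 0.47·0.53)]² / 0.15² = (1.355 + 0.575)² / 0.0225 ≈ 165.5, rounded up to 166.

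166 / 0.85 = 195.3, rounded up to 196 per arm, or 392 in total. This matches the plan. The sample size is not in dispute.

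**2. Reach of one break.**
- Two labels: learning that one letter is active (or placebo) settles the other by elimination, so 196 + 196 = 392 assignments are decodable.
- One code per participant: a break discloses 1 of 392.

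The 392 is a maximum. It applies only to someone who has the decoded letter and also the letters of all participants. By envelope storage, Hong Kong Baptist University holds 100 + 192 = 292 and the Chinese University of Hong Kong 100, so no single site sees all 392. Only assessments made after a break can be affected.

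**3. Fixed blocks.** This concerns predicting letters, not arms. In a 1:1 block of size 2m, letters become certain once one letter is used up. The expected number of such letters is 2m/(m + 1), so the expected share is 1/(m + 1) for someone who sees every letter and knows the block size.

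| Assumption | Even block sizes that fit | Share of letters certain |
|---|---|---|
| Blocks completed within each envelope lot (100, 100, 192; greatest common divisor 4) | 2 or 4 | 1/2 = 50% or 1/3 = 33% |
| One list of 392, split afterwards for storage | 2 and 4, but also for example 8 or 14 | for 8: 1/5 = 20%; for 14: 1/8 = 12.5% |

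Direct check for size 4: the fourth letter is always known, and the third is known with probability 1/3, so (1 + 1/3)/4 = 33%.

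The article does not say which assumption holds, so the last column is a range and not a finding about this trial.

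**The case against.** Several objections stand and limit the point.

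- **Exposure is not automatic.** A reader might infer that one break unblinds all 392 participants. The article does not support that. The person told must also see the labels, a participant must learn what their own letter means, and assessments already made are untouched.
- **A guess is not a break.** A reader might infer that guessing the letter is as damaging. The article says placebo and active drug match in packaging, appearance, colour and taste, and nothing in it shows a distinguishing effect. Pooling outcomes by letter would help a guesser: at 47% against 32%, the better-looking letter is the active one with probability about 0.83 at 20 participants per letter and 0.94 at 50. But someone would have to do that pooling, the 32% is an assumption, and the result is a probability, not knowledge.
- **Letters are not shown to be easily predicted.** The block size is unstated. Hong Kong Baptist University runs two of the three centres, each centre has its own research assistant, and none of them need see a whole block. Recruitment and evaluation rest with blinded practitioners, separate from envelope opening. Predicting a letter does not give the arm while the code is intact.
- **The principal investigators' role is limited in the text.** They keep the code and receive reports. The article does not say that they consulted the code or run the meetings.
- **Breaks are restricted and recorded.** The trigger is narrow and the date goes in the CRF. Fuller unblinding logistics may sit in the full protocol.

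The last objection does not remove the core. The two-label scheme and the custody of the code are stated rules, not omitted details. A participant number printed beside the letter would not cure the problem.

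**Conclusion.** The point holds as a design weakness. Two arm-level labels mean that a code break for one participant reveals the arm of every participant whose label is known to the person told: at most 392 of 392, against 1 of 392 with participant-level codes. Keeping the code with the principal investigators, who receive ongoing compliance and adverse-event reports, adds avoidable risk through to the final analysis. The fixed block size is a secondary aggravation whose size depends on unstated facts.

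The documents do not support concluding that blinding was lost. No code break is reported. According to Trial status, recruitment ran from 8 November 2018 to 29 October 2020 and the last follow-up was on 17 February 2021. If no break occurred, the main route to bias described here was never opened, and what remains is custody of the code and blinding of the analyst.

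**What to change.** **In the plan.** Label each supply with its unique randomisation number (001–392) in place of A or B. Provide one code-break envelope per number, held by someone outside the study team. The cost is different label printing and code handling. The trigger for breaking the code is taken as given.

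**For the completed trial, before analysis:**
1. Move the code to a holder independent of the principal investigators and the analyst.
2. Re-letter the two groups in the analysis data set, so that A and B as used in the clinics carry no information.
3. List the date of every code break, from the CRF entries already required; state explicitly if there were none.
4. If a break occurred, add a GAI sensitivity analysis that excludes assessments made after it.

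The cost is one listing and at most one sensitivity analysis. That analysis would be less precise than the primary one, because it drops later assessments.

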### Recruitment

The recruitment of the study is via the press conferences, announcements on university website, advertisements on local newspapers or Facebook, promotion posters and leaflets, and specialist’s referral. People who are interested in the trial can contact the researchers by telephone or e-mail. Researchers will conduct preliminary screening on the phone and invite these potential candidates to come to the clinics to have a further screening face to face. Chinese medicine practitioners will be responsible for conducting the screening and explaining the details of the study, such as content, arrangement, and possible risks etc. The eligible participants will be invited to join the study after signing the informed consent form.

